## Abstract

**Background:**

Patients with chronic idiopathic axonal polyneuropathy (CIAP) can have neuropathic pain that significantly impacts quality of life. Oral neuropathic pain medication often has insufficient pain relief and side effects. Topical phenytoin cream could circumvent these limitations.

The primary objectives of this trial are to evaluate (1) efficacy in pain reduction and (2) safety of phenytoin cream in patients with painful CIAP. The main secondary objective is to explore the usefulness of a double-blind placebo-controlled response test (DOBRET) to identify responders to sustained pain relief with phenytoin cream.

**Methods:**

This 6-week, enriched enrollment randomized double-blind, placebo-controlled triple cross-over trial compares phenytoin 20%, 10% and placebo cream in 48 participants with painful CIAP. Enriched enrollment is based on a positive DOBRET in 48 participants who experience within 30 minutes ≥2 points pain reduction on the 11-point numerical rating scale (NRS) in the phenytoin 10% cream applied area and ≥1 point difference in pain reduction on the NRS between phenytoin 10% and placebo cream applied area, in favour of the former. To explore whether DOBRET has predictive value for sustained pain relief, 24 DOBRET-negative participants will be included.

An open-label extension phase is offered with phenytoin 20% cream for up to one year, to study long-term safety.

The main inclusion criteria are a diagnosis of CIAP and symmetrical neuropathic pain with a mean weekly pain score of ≥4 and <10 on the NRS.

The primary outcome is the mean difference between phenytoin 20% versus placebo cream in 7-day average pain intensity, as measured by the NRS, over week 2 in DOBRET positive participants.

Key secondary outcomes include the mean difference in pain intensity between phenytoin 10% and phenytoin 20% cream, and between phenytoin 10% and placebo cream. Furthermore, differences between the 3 interventions will be evaluated on the Neuropathic Pain Symptom Inventory, EuroQol EQ5-5D-5L, and evaluation of adverse events.

**Discussion:**

This study will provide evidence on the efficacy and safety of phenytoin cream in patients with painful CIAP and will give insight into the usefulness of DOBRET as a way of personalized medicine to identify responders to sustained pain relief with phenytoin cream.

**Trial registration:**

ClinicalTrials.gov NCT04647877. Registered on 1 December 2020.

## Administrative information

Note: the numbers in curly brackets in this protocol refer to the SPIRIT checklist item numbers. The order of the items has been modified to group similar items (see http://www.equator-network.org/reporting-guidelines/spirit-2013-statement-defining-standard-protocol-items-for-clinical-trials/).

## Introduction

### Background and rationale {6a}

Chronic idiopathic axonal polyneuropathy (CIAP) is a slowly progressive distal symmetric sensory or sensorimotor polyneuropathy without a known cause [1]. Sensory or sensorimotor symptoms start in the toes and gradually extend to the feet or lower legs, and sometimes involve the hands. Almost all patients experience negative sensory symptoms such as numbness and tightness (as if something is wrapped tightly around the foot or leg giving an unpleasant tense feeling of compression). Between 27–60% of CIAP patients report neuropathic pain in the feet sometimes extending into the lower legs, which impacts quality of life, work, sleep, and can induce or worsen depression in patients with polyneuropathy [2–5]. Painful positive sensory symptoms include tingling, pins and needles, burning. Up till now, no randomized controlled trials have been conducted in patients suffering from (painful) CIAP [1]. However, current first-line pharmacological treatment recommendations for painful polyneuropathy in general are oral tricyclic antidepressants, serotonin-noradrenaline reuptake inhibitors, and gabapentinoids [6–9]. A majority of patients have insufficient analgesic effect from currently available oral pain medication, but do experience mild, moderate or unacceptable side effects that hamper compliance to treatment [8, 10]. The number needed to treat (NNT) for oral tricyclic antidepressants, serotonin-noradrenaline reuptake inhibitors, and gabapentinoids varies between 3.6 and 7.7 for a treatment response of ≥ 50% pain reduction [8]. The number needed to harm (NNH) for treatment by the maximal daily dose ranges between 2.6 and 10.4 [10]. Especially in elderly patients, pharmacological management can be challenging due to age-related body changes affecting drug pharmacokinetics, and due to polypharmacy causing more frequent drug-related side effects, with greater potential to harm [11].

Thus, new treatment strategies are needed to improve neuropathic pain management with less side effects. Topical analgesics are an interesting therapeutic option, because they might influence only the nerve endings in the epidermis without reaching the bloodstream, thus resulting in fewer or no systemic side effects [12, 13]. Topical analgesics used to treat neuropathic pain are lidocaine 5% patch and capsaicin 8% patch, notwithstanding very low to moderate quality of the evidence, and thus are proposed as second-line treatments [8, 9, 14, 15]. Topical use of analgesics seems especially feasible in localized neuropathic pain, which has been defined as neuropathic pain characterized by consistent and circumscribed area(s) of maximum pain [16].

The newly developed phenytoin cream could fulfil the need of a novel neuropathic pain treatment [17–21]. Phenytoin 5% and 10% cream demonstrated analgesic effect in patients with neuropathic pain in the absence of systemic side effects, and there are some indications that 10% cream is more effective compared to 5% cream [17–19]. In daily practice observational studies phenytoin 20% cream was effective and neither side effects nor detectable phenytoin plasma levels were reported [22, 23]. No randomized clinical trial has compared phenytoin cream versus placebo nor compared phenytoin 20% versus 10% cream.

A randomized clinical trial evaluating topical clonidine in diabetic neuropathic pain patients found a more profound pain reduction when patients experienced more burning sensation after application of topical capsaicin, suggesting that treatment success might be dependent on the preservation of signal transduction of sensory nerves from the skin to the brain [24]. An alternative elegant way to evaluate the integrity of sensory nerves is to determine the analgesic effect of the active cream within 30 min of application in a double-blind placebo-controlled response test (DOBRET) [21]. A DOBRET is especially feasible in symmetrical polyneuropathy and localized neuropathic pain such as in painful CIAP, because a proper comparison can be made after application of the active cream on for example one foot and placebo cream on the other foot. With the DOBRET, initial responders to the active cream can be identified. Also, local allergic reactions or transient aggravation of pain can be ruled out. Given the absence of trials evaluating analgesics in patients with CIAP, we will conduct a DOBRET enriched enrollment randomized double-blind placebo-controlled triple cross-over trial to evaluate the effectiveness and safety of phenytoin cream in painful CIAP. After the 6-week cross-over trial, participants are offered to use phenytoin 20% cream in the 1-year open-label period, to evaluate long-term pain reduction and safety.

### Objectives {7}

The primary objectives are to evaluate (1) efficacy in pain reduction and (2) safety of phenytoin cream in participants with painful CIAP. Safety is evaluated by asking for local and systemic side effects, and by measuring phenytoin plasma levels. Possible reported systemic side effects will be correlated with phenytoin plasma levels. The secondary main objective is to explore the usefulness of DOBRET as a way of personalized medicine to identify responders to sustained pain relief with phenytoin cream.

### Trial design {8}

This is a 6-week single-centre, enriched enrollment randomized double-blind, placebo-controlled triple cross-over trial to evaluate the efficacy and safety of phenytoin cream (20% and 10%) versus placebo in 48 participants with painful CIAP. The enriched enrollment is based on a positive double-blind placebo-controlled response test (DOBRET) in 48 participants who experience within 30 minutes at least 2 points pain reduction on the 11-point numerical rating scale (NRS) on the phenytoin 10% cream applied area and at least 1 point difference in pain reduction on the NRS between phenytoin 10% and placebo cream applied area, in favour of the former. To explore to which extent and which responder definition for the DOBRET has a predictive value for sustained pain relief, an additional 24 DOBRET negative participants will be included.

Participants will be randomly allocated to one of the 6 possible intervention sequences. Participants and investigators will be blinded. The duration of each treatment period is 2 weeks. Participants will cross-over two times to each of the other treatments. The study does not have wash-out periods between treatments, because the mean duration of the analgesic effect after an application is expected to be less than 9 h [19]. A flow chart of the study is presented in Fig. 1.

**Fig. 1 Fig1:**
[figure not shown]
Flow chart. DB, double-blind; DOBRET, double-blind placebo-controlled response test

## Methods: participants, interventions and outcomes

### Study setting {9}

This monocentric trial will be executed in the University Medical Center Utrecht (UMCU), the Netherlands.

### Eligibility criteria {10}

Patients will be recruited from the UMCU neurology outpatient clinic. When patients from outside of the UMCU want to participate, a consultation for the confirmatory diagnosis will be carried out. Inclusion criteria are age ≥ 40 years; confirmed CIAP diagnosis [25]; presence of ≥3 months localized neuropathic pain in two symmetrical areas of feet/lower legs; with a pain intensity difference of ≤1 point on the NRS; ≥1 h daily pain; with a weekly mean pain score between ≥4 and <10 on the NRS at study entry; Douleur Neuropathique 4 questions (DN4) score ≥4 [26]; and no changes in neuropathic pain medication of ≥1 month. The main exclusion criteria are other (neuropathic) pain conditions; open wounds in the neuropathic pain area; current use of topical analgesics; hypersensitivity to study drugs; oral use of phenytoin and (planned) pregnancy. The primary investigator ([name]) and the two research physicians ([name] and [name]) will screen patients for eligibility. Eligible patients who are willing to participate will be recruited for the trial.

### Who will take informed consent? {26a}

Upon confirmation of willingness to participate, the eligible patient will be sent the patient information regarding the study and the informed consent form. One week later the research physician will phone the patient to answer any questions and will ask if the patient is willing to participate. Upon the patient’s agreement, the research physician will obtain the patients’ written informed consent at the first study visit.

### Additional consent provisions for collection and use of participant data and biological specimens {26b}

In the patient information letter, the trial outline is presented. During the trial, at the second visit blood withdrawal will be performed to determine phenytoin plasma concentrations in patients who applied 10% and 20% cream, in order to evaluate the safety of topical phenytoin. Possible reported systemic side effects will be correlated with phenytoin plasma levels. Plasma phenytoin analyses will be performed after data analyses to maintain blinding. The written consent form contains statements that the participant has read the information letter, could ask questions, had enough time of reflection on the trial, gives permission of collection and use of participant data, and can withdraw from the trial at any time.

## Interventions

### Explanation for the choice of comparators {6b}

In this cross-over, double-blind trial the comparator will be placebo cream applied 2 to 4 times daily according to the duration of effect. The active and placebo cream have the same white appearance and neutral smell. All participants will receive this treatment during a 2-week treatment period. Placebo cream is chosen to identify the magnitude of pain reduction attributable to the active interventions. Furthermore, a placebo cream is also used in the DOBRET to explore the predictive value of this test [21].

### Intervention description {11a}

All participants will receive placebo, phenytoin 10% and phenytoin 20% cream, each during a period of 2 weeks. The participant will be instructed to apply the cream 2 to 4 times a day with a maximum of 1.5 g per application, measured in Finger Tip Units (FTU).

One FTU is defined as the amount of cream expressed from a tube with a 5 mm diameter nozzle, applied from the distal skin crease to the tip of the index finger, which amounts to approximately 0.5 g (see Fig. 2). The number of daily applications depends on the duration of the analgesic effect and the amount of cream depends on the size of the painful areas, e.g. both feet 1 FTU, and both feet and lower legs 3 FTU. The participant can apply the cream with bare hands, and then wash the hands after each application. After the double-blind period participants are invited to use phenytoin 20% cream in the 1-year open-label extension phase, to study the long-term pain reduction and safety.

**Fig. 2 Fig2:**
[figure not shown]
Finger Tip Unit

### Criteria for discontinuing or modifying allocated interventions {11b}

Participants are allowed to drop out at any time without giving a reason. Other criteria are serious adverse event (SAE), unacceptable adverse event (AE), and/or protocol violation, including use of prohibited pain medication.

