### Relevant concomitant care permitted or prohibited during the trial {11d}

Participants can continue their neuropathic pain medication when the dosage has been stable for at least one month. Acetaminophen and non-steroid anti-inflammatory drugs are allowed as escape medication for acute pain other than the neuropathic pain due to CIAP. Oral phenytoin, opiates and other topical analgesics are not allowed. Use of escape medication will be recorded in the on a daily base.

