#### Secondary outcomes

All secondary outcomes are evaluated for phenytoin 20% versus 10% versus placebo cream in DOBRET positive, negative and all participants.

The change between baseline and week 2 for each intervention is assessed for:Pain intensity measured on theNRSNeuropathic Pain Symptom Inventory (NPSI), evaluating on the NRS neuropathic pain characteristics [27]NRS for the 3 worst pain characteristics≥30% and ≥50% improvement on the NRS compared to placebo within one participant, reflecting at least moderate and at least substantial improvement [28]Patient-reported percentage of pain reduction at the end of the second week of each interventionOnset of the analgesic effect after applicationDuration of the analgesic effect after one applicationDaily number of cream applicationsUse of escape pain medicationQuality of life measured on thesubscales of the Brief Pain Inventory (sBPI), evaluating on the NRS pain interference regarding general activity, mood, walking ability, normal work, relations with other people, sleep, and enjoyment of life [29]EQ5-5D-5L, measuring the health status on the visual analogue scale, and on a 5-point scale pain/discomfort, anxiety/depression, mobility, self-care and usual activities [30]Patient Global Impression of Change Scale (PGIC), measured on a 7-point scale [31]To evaluate the safety and tolerability of phenytoin 10% and 20% creamTolerability is defined as time-to-discontinuation of an assigned treatment since randomization.Safety is based on the safety assessments including physical examinations, clinical laboratory evaluations, vital signs and frequency of AEs or SAEs. (S)AEs will be categorized according to the Common Terminology Criteria for Adverse Events and will be rated for severity and association with the study drug.Detection of phenytoin in plasmaPredictive value of DOBRET in sustained pain reduction due to phenytoin creamTo evaluate the correlation between the PCS and the pain-reducing effect of topical phenytoin

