### Sample size {14}

We hypothesized a mean difference of 2 points on the NRS between placebo and the 20% cream (π1), and a mean difference of 1 point between 20% and 10% cream (π2). Based on preliminary data [21], we assumed for both treatment effects a standard deviation of 3.3 (standardized effect sizes: π1 = 0.61, π2 = 0.30). Using the same dataset, we conservatively assumed a correlation between NRS scores within participants (intraclass correlation) of 0.3. Seven participants per sequence (e.g. placebo–20%–10%, or 10%–placebo–20%) would be required to achieve 80% power and a two-sided significance level of 5% (= 7 × 6 sequences = 42 total sample size) [32]. Assuming a 10% drop-out rate, we will enrol 8 responding participants per group or 48 in total. DOBRET-negative participants are assumed to exhibit a mean difference of 1.5 point s (SD 4) on the NRS between placebo and the 20% cream, where 1 in 3 patients are assumed to be DOBRET-negative. This would result in a pooled overall treatment effect across DOBRET negative and positive participants of 1.83 (SD 4). Enrolling 24 DOBRET-negative and 48 DOBRET-positive participants would result in a power of 84% for the overall population.

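### The secondary tolerability outcome counts stopping a cream without restricting the cause, so stops from failed pain relief can bias its comparison with placebo towards phenytoin

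*Protocol article*

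**What the plan says.** Secondary outcomes (Outcomes {12}) defines tolerability as the time from randomization to stopping an assigned treatment. The definition does not limit which stops count. The same section fixes the comparison: "All secondary outcomes are evaluated for phenytoin 20% versus 10% versus placebo cream in DOBRET positive, negative and all participants".

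The routes to stopping are in Criteria for discontinuing or modifying allocated interventions {11b}. The first is "Participants are allowed to drop out at any time without giving a reason". The rest follow in one sentence: "Other criteria are serious adverse event (SAE), unacceptable adverse event (AE), and/or protocol violation, including use of prohibited pain medication".

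Relevant concomitant care {11d} says which analgesics are prohibited: "Oral phenytoin, opiates and other topical analgesics are not allowed". Stable neuropathic pain medication may continue. Escape medication is limited: "Acetaminophen and non-steroid anti-inflammatory drugs are allowed as escape medication for acute pain other than the neuropathic pain due to CIAP".

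Safety is a separate item in the list of secondary outcomes: "Safety is based on the safety assessments including physical examinations, clinical laboratory evaluations, vital signs and frequency of AEs or SAEs". Objectives {7} makes safety a primary objective, to be judged from reported local and systemic side effects and from phenytoin plasma levels. Time to discontinuation is not part of that description.

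**The concern.** A tolerability outcome should register harm or discomfort from the cream. As worded, this one also registers participants who leave, or take a prohibited analgesic, because the cream does not help. Section {11d} lists no added medication for unrelieved CIAP pain, so a participant on an ineffective cream can bear the pain, withdraw, or take something not allowed. The last two can end treatment under {11b}, and would then count as tolerability events.

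Under the trial's own hypotheses these stops should be most frequent on placebo. They would then offset stops caused by adverse events on phenytoin. A null or favourable result could be read as good tolerability when it partly reflects placebo failure.

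**Working it through.** The documents give no tolerability rate, hazard ratio or power for this outcome, so there is no stated result to reproduce. The check has two parts.

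**1. Does the event depend on efficacy?**
- Definition (Secondary outcomes): stopping, with no cause named.
- Routes ({11b}): unexplained withdrawal, SAE, unacceptable AE, and protocol violation including prohibited pain medication.
- Expected efficacy (Sample size {14}): 2 NRS points between 20% cream and placebo and 1 point between 20% and 10%, hence 2 − 1 = 1 point between 10% and placebo.

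Two of the routes can follow from poor relief, and relief is expected to be worst on placebo. Nothing in the article removes those stops from the tolerability event.

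**2. How large could the effect be?**

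The only relevant figure is the overall drop-out: "Assuming a 10% drop-out rate, we will enrol 8 responding participants per group or 48 in total". It reproduces: 42 / (1 − 0.10) = 46.7, so 47, rounded up to 8 × 6 = 48. It is not split by cause or by cream.

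Assume that drop-out is spread evenly over the three periods and that each drop-out is a stop of the current cream:
- per-period stopping = 1 − 0.90^(1/3) = 0.0345, about 3.5%
- in 48 participants: 48 × 0.0345 = about 1.7 stops per period.

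Treat causes as mutually exclusive, so that percentages add. Let *a* be the excess of adverse-event stops on phenytoin over placebo, and *f* the excess of failed-relief stops on placebo over phenytoin. The visible all-cause difference is *a* − *f*.

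Illustration with assumed rates:

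| | 20% cream | Placebo | Difference |
|---|---|---|---|
| Adverse-event stops | 3% | 0% | 3 points |
| Failed-relief stops | 0% | 3% | −3 points |
| All stops | 3% | 3% | 0 points |

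If the 10% cream also has 3%, overall stopping is 1 − 0.97³ = 8.7%, within the planned 10%. In people, 3% is 0.03 × 48 = 1.4 DOBRET-positive participants, or 0.03 × 72 = 2.2 of all participants.

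The range follows from *a* − *f*:
- *f* = 0 (equal failed-relief stops on both creams): the absolute difference is unbiased.
- *f* between 0 and *a*: the excess is understated.
- *f* = *a*: it disappears.
- *f* greater than *a*: it reverses.

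**The case against.** The strongest reply is that all-cause discontinuation is a legitimate outcome, openly stated, and that handling of causes, censoring and competing events is commonly left to a full protocol or SAP. The part about analysis detail stands: the absence of censoring rules from a journal article is no finding. But the event itself is defined here, without restriction, and compared across creams. All-cause stopping measures retention or acceptability, which combines benefit and harm. Calling it tolerability is what misleads.

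Several limits on the mechanism also stand. "The duration of each treatment period is 2 weeks", everyone is due to receive the other creams, and background pain medication continues, so failed-relief stops may be few. A prohibited drug may be taken for unrelated pain. Section {11b} does not say that prohibited medication always ends treatment.

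A reader might go further and infer that the primary safety objective is biased, or that intolerance of phenytoin would go unseen. The documents do not support this. Objectives {7} bases safety on side effects and plasma levels. AEs and SAEs are graded for severity and for association with the study drug (Secondary outcomes) and are asked about at each visit after a treatment period (section {18a}). An unacceptable adverse event that ends treatment should therefore appear in that record.

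A reader might also suppose that a large excess is hidden, for example 6% + 2% = 8% on 20% cream against 1% + 7% = 8% on placebo, which conceals 5 points. Even with no stops on 10% cream, that implies 1 − 0.92² = 15% overall, and with 8% there too, 1 − 0.92³ = 22%. Both exceed the planned 10%.

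**Conclusion.** The point holds for the secondary tolerability outcome only. As defined, it mixes lack of efficacy with intolerance, and the likely bias favours phenytoin if phenytoin relieves pain better than placebo. At the planned drop-out the numbers are small: about 1.7 stops per period in 48 participants, so one or two failed-relief stops on placebo could cancel a similar number of adverse-event stops on phenytoin.

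This rests on three assumptions that the documents do not settle: that stops are spread evenly over periods, that some of them follow from poor relief, and that these are more frequent on placebo. If failed-relief stops are equal across creams, the absolute difference is unbiased.

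**What to change.** In Secondary outcomes:
- Define the tolerability event as stopping a cream because of an adverse event.
- Treat stops for other reasons as competing events, and report them by cream and reason.
- Keep all-cause discontinuation as a supplementary outcome under that name.
- In a sensitivity analysis, count stops without a stated reason as adverse-event stops, since {11b} lets participants leave without giving one.

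The cost is a change of wording and a reason-for-stopping field at the existing visits. The downside is fewer events per cream and some unknown reasons, so cause-specific results will carry some misclassification. No change to the stopping or medication rules is proposed.
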